## Abstract

**Background:**

Measuring vital signs (VS) is an important aspect of clinical care but is time-consuming and requires multiple pieces of equipment and trained staff. Interest in the contactless measurement of VS has grown since the COVID-19 pandemic, including in nonclinical situations. Lifelight is an app being developed as a medical device for the contactless measurement of VS using remote photoplethysmography (rPPG) via the camera on smart devices. The VISION-D (Measurement of Vital Signs by Lifelight Software in Comparison to the Standard of Care—Development) and VISION-V (Validation) studies demonstrated the accuracy of Lifelight compared with standard-of-care measurement of blood pressure, pulse rate, and respiratory rate, supporting the certification of Lifelight as a class I Conformité Européenne (CE) medical device.

**Objective:**

To support further development of the Lifelight app, the observational VISION Multisite Development (VISION-MD) study is collecting high-quality data from a broad range of patients, including those with VS measurements outside the normal healthy range and patients who are critically ill.

**Methods:**

The study is recruiting adults (aged ≥16 years) who are inpatients (some critically ill), outpatients, and healthy volunteers, aiming to cover a broad range of normal and clinically relevant VS values; there are no exclusion criteria. High-resolution 60-second videos of the face are recorded by the Lifelight app while simultaneously measuring VS using standard-of-care methods (automated sphygmomanometer for blood pressure; finger clip sensor for pulse rate and oxygen saturation; manual counting of respiratory rate). Feedback from patients and nurses who use Lifelight is collected via a questionnaire. Data to estimate the cost-effectiveness of Lifelight compared with standard-of-care VS measurement are also being collected. A new method for rPPG signal processing is currently being developed, based on the identification of small areas of high-quality signals in each individual. Anticipated recruitment is 1950 participants, with the expectation that data from approximately 1700 will be used for software development. Data from 250 participants will be retained to test the performance of Lifelight against predefined performance targets.

**Results:**

Recruitment began in May 2021 but was hindered by the restrictions instigated during the COVID-19 pandemic. The development of data processing methodology is in progress. The data for analysis will become available from September 2022, and the algorithms will be refined continuously to improve clinical accuracy. The performance of Lifelight compared with that of the standard-of-care measurement of VS will then be tested. Recruitment will resume if further data are required. The analyses are expected to be completed in early 2023.

**Conclusions:**

This study will support the refinement of data collection and processing toward the development of a robust app that is suitable for routine clinical use.

**Trial Registration:**

ClinicalTrials.gov NCT04763746; https://clinicaltrials.gov/ct2/show/NCT04763746

**International Registered Report Identifier (IRRID):**

DERR1-10.2196/41533

## Introduction

The measurement of vital signs (VS) provides important information about a patient's health and, importantly, a change in VS may herald a deterioration in health [1]. Despite the importance of VS to inform clinical decision-making, the accuracy and timeliness of measurement are in need of improvement [2-4]. However, the measurement of VS requires using multiple pieces of equipment that need to be calibrated regularly and is time-consuming. It may also be uncomfortable and stressful for patients, potentially compromising the utility of the information obtained. Standard-of-care medical equipment is not suitable for patients who require regular measurement of VS in the home or community setting to monitor long-term health conditions because of cost, the complexity of the measuring processes, and the need for calibration of equipment. A study of 725 patients reported that while 53% followed at least 10 of the recommended steps necessary for accurate blood pressure (BP) measurement at home, only 1% followed all 15 recommendations [5]. Thus, home measurement of VS is important—and respiratory rate and pulse rate in particular—but requires several pieces of equipment (BP monitor and pulse oximeter) and for patients to be educated in best practices. The COVID-19 pandemic highlighted the need for remote or contactless VS measurement to reduce the risk of infection, which can be operated by people without specific medical training. The shift away from face-to-face to digital consultations during the pandemic also points to the need for easy but accurate measurement of VS.

Photoplethysmography (PPG) is an optical technique based on the measurement of the light reflected from the skin surface, which changes due to volumetric changes in the facial blood vessels; small variations in perfusion provide valuable information about the cardiovascular system [6]. PPG has been used to measure pulse rate [7,8], oxygen saturation [9], BP [10,11], and respiratory rate [7,12] and to detect atrial fibrillation [13].

Lifelight (Xim Ltd) is an app being developed for the contactless measurement of VS using remote PPG (rPPG) via the camera on smart devices such as phones and tablets. The app captures the average color of the region of interest 30 times every second for 60 seconds and sends this as red, green, and blue values to the server for further processing. VS values are obtained from the green channel.

The VISION-D (Measurement of Vital Signs by Lifelight Software in Comparison to the Standard of Care-Development) study measured VS in 8585 patients and healthy volunteers simultaneously using Lifelight and standard-of-care methods. The data were used for machine learning to improve the accuracy of the Lifelight algorithms used to calculate VS. The smaller VISION-V (Measurement of Vital Signs by Lifelight Software in Comparison to the Standard of Care–Validation) study demonstrated the accuracy of the Lifelight app compared with standard-of-care methods for measuring pulse rate, respiratory rate, and diastolic BP [14], providing the basis for the current class I Conformité Européenne (CE) registration [15]. However, some of the methods used in the VISION-V study differed from the procedures described in the standard for BP measurement (ISO81060-2) because of the novel nature of the Lifelight technology. Furthermore, these early studies did not include participants with BP values across the full range likely to be encountered in clinical practice.

To further improve the accuracy of Lifelight, the Measurement of Vital Signs by Lifelight Software in Comparison to the Standard of Care–Multisite Development (VISION-MD) study is collecting data from a wide range of outpatients, inpatients, and patients who are critically ill, and across the full range of skin tones, for use in machine learning. In VISION-D and VISION-V, full-face videos were recorded, but a high proportion of data were not usable. Thus, high-resolution full-face videos are being recorded to maximize the opportunity for machine learning. These data will also be used to evaluate alternative methods of defining the region of interest, as the full face includes areas that are not relevant (eg, areas covered by facial hair and areas that illicit a poor signal).

Given that only a small proportion of the raw video signal is relevant for rPPG measurement of VS (1%-2%), we are developing ways to enhance data collection and signal processing. Video recordings will be of higher resolution than those in the VISION-V and VISION-D studies, and data processing is focusing on the midface region (cheeks, nose, and top of the lip), rather than the whole face; these areas are computationally efficient for rPPG because of their large area and good-quality signal [16] but are not likely to be affected by autoregulation of cerebral blood flow (which discounts the forehead) [17]. We are also developing a method to identify small regions of interest in the midface in each participant where signal quality is the highest. This approach is expected to overcome some of the challenges of rPPG for routine clinical use, such as positioning of the participant relative to the light source.

VISION-MD (Clinicaltrials.gov NCT04763746) aims to advance the development and accuracy of the Lifelight app as a noninvasive and easy-to-use device to measure VS in hospitals and the community. The study will collect data from a broad range of patients to further develop the accuracy of Lifelight to a level sufficient for clinical applications, including screening and monitoring of cardiovascular disease. The initial data collected are being used for machine learning; later data will be used to test the accuracy of Lifelight compared with standard-of-care measurement of VS.

Thus, the primary objective of VISION-MD is to further develop the Lifelight algorithms across extensive clinical ranges, including critically ill patients and in patients with different skin tones. Secondary objectives are: (1) to improve and test the efficacy of Lifelight estimates for BP, pulse rate, respiratory rate, and oxygen saturation in multiple clinical settings (eg, critical care, outpatient clinics, and general hospital wards); (2) to evaluate the impact of variables on the accuracy of Lifelight VS measurements (eg, age, sex, temperature, health condition, medication, skin tone, and ambient lighting); (3) to understand the health economic potential of Lifelight; and (4) to compare the patients’ experience of current contact-based methods for measuring VS and Lifelight and to evaluate the patients’ acceptance and appetite for Lifelight.

## Methods

### Ethics Approval

The VISION-MD protocol was approved by the South Berkshire Research Ethics Committee on November 24, 2020 (20/SC/0432). Before the study started, the initial study protocol was approved by Health Research Authority (HRA) Wales on January 18, 2021 (IRAS 289242). HRA Wales has also approved subsequent protocol amendments.

### Participants and Recruitment

Participants are being recruited from multiple venues across Portsmouth Hospitals University NHS Trust, Barts Health NHS Trust, London, and from the community in London and Portsmouth (eg, religious places, community centers, offices, patient events, waiting areas in general practices, academic institutions, sports facilities, and care homes). The participants are inpatients, outpatients, friends and family of patients, visitors, hospital staff members, and the general public. The study staff approach inpatients during their hospital stay and outpatients while waiting for appointments. For adults lacking capacity (eg, critically ill patients), the next of kin are contacted by telephone. In addition, ethics-approved advertising materials are disseminated to Trust staff by email and in meetings, and posters are displayed in staff, patient, and public areas.

Inclusion criteria include individuals aged 16 years and older, sufficiently conversant in the English language, and able and willing to comply with all study requirements and to provide informed consent (either themselves or empowered by law to provide it). There are no exclusion criteria. Eligible potential participants are provided with an ethics-approved participant information sheet explaining the study aims, what is involved, and the requirements for participation; members of the team are available to discuss the study with interested individuals. Informed consent is obtained electronically using Research Electronic Data Capture (REDCap), a secure National Health Service (NHS)–compliant web-based platform for survey and database management (project-redcap-org). For adults lacking capacity, informed consent is obtained from a nominated consultee (next of kin or a doctor not involved in the study). Participation in the study is entirely voluntary, refusal to participate does not incur a penalty or loss of medical benefits, and participants may withdraw from the study at any time.

Recruitment started in May 2021 but was compromised by restrictions implemented during the COVID-19 pandemic to limit access to hospitals by the general public. Protocol amendments were made to increase community recruitment in light of these issues. Target recruitment is approximately 1950 participants to generate measurements for use in the initial training data set and for performance testing. However, the final sample size will depend on the incremental improvement in accuracy of the Lifelight algorithm and therefore cannot be predicted (see Sample Size section). The study will continue until the accuracy of Lifelight for measuring VS is sufficient for various clinical use cases.

### Study Procedures

#### Premeasurement observations

A brief set of demographic and medical history questions are asked, limited to the presence or absence of conditions that might affect skin perfusion and pigmentation and cardiovascular processes and any prescription medicines for these conditions. The study staff record a set of premeasurement observations and the presence or absence of sweat on the participant’s face; any facial hair on the cheeks; tattoos, jewelry, birthmarks, scars, or other features on the face; the use of foundation or concealer; and the position of the participant (seated, prone, supine, or lying on one side).

#### VS measurement

The study staff ensure that participants have been at rest for at least 10 minutes before VS measurement starts and that they have not consumed any food or drink in the previous 30 minutes (other than intravenous fluids or nasogastric feeding). In each study session, VS is measured as per the subprotocol using the standard-of-care equipment while simultaneously capturing a video of the participant’s face using the Data Collect app running on a tablet (standard iPad 9.7, 2018) positioned approximately 1 m away and angled toward the participant’s face. Controls and instructions on the device start and stop the 60-second video recording. Background luminosity is measured using a handheld lux meter. The study staff have been briefed on the optimum Lifelight measurement conditions. Recordings are repeated once or twice, as set out in Table 1. The app does not return any measurements to the user or participant.

VS measurements are taken and coordinated by 2 nurses, one of whom announces the start and finish of the recording period on the Data Collect app. BP is measured using a standard clinical automatic sphygmomanometer with an appropriately sized cuff (width at least two-thirds of upper arm length) on the participant’s nondominant upper arm (unless contraindicated) or via an arterial line if fitted. BP is recorded at the start of the recording period. A standard clinical finger clip sensor for the measurement of oxygen saturation and pulse rate is placed on a finger on the opposite side of the body to the sphygmomanometer. Oxygen saturation and pulse rate are measured at 0, 30, and 60 seconds of the recording period and averaged. Respiratory rate is determined manually by counting chest rises throughout the 60-second period. The nurse may place their hand on the participant’s chest to increase the accuracy of manual counting but being mindful not to obscure the camera’s line of sight.

Each study session takes approximately 30 minutes. Once the measurements are completed, the study staff complete the postmeasurement observation questions relating to how much the participant moved, their position, whether they were wearing glasses, any hairstyle or other item (eg, face covering) that obscured any part of their face during the recording, and whether the software reported “face not found” at any point during the recording.

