### Performance Targets

The accuracy of Lifelight using the training data generated in VISION-D was sufficient to support the certification of Lifelight as a class I CE medical device [15]. However, the accuracy needs to be improved further for use in routine clinical practice. Table 2 lists the performance targets for Lifelight; training data collected during VISION-MD will support the progress toward these targets.

**Table 2 table2:** Performance (accuracy) targets for Lifelight.

Vital signs	Accuracy target	Basis for target
Blood pressure	SBP^a^ can be measured with standard deviation ≤8 mm Hg British Hypertension Society Grade C for SBP measurement	ISO81060-2^b^ for blood pressure cuffs [19]
Pulse rate	Root mean square error of ≤3 beats per minute	Most common accuracy of CE^c^-marked commercially available devices
Respiratory rate	Maximum error tolerance of 5 breaths per minute	Accuracy of Philips Health watch, a CE-marked contact-based photoplethysmography device
Oxygen saturation	Maximum error tolerance of 4%	ISO80601-2-61 standard for pulse oximeters [20]

^a^SBP: systolic blood pressure.

^b^ISO: International Organization for Standardization.

^c^CE: Conformité Européenne.

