### Data Analysis

The training data will be used to further develop the signal extraction and processing methodology. The test data will subsequently be used to determine the performance of Lifelight against the targets set out in Table 2.

All statistical analyses will be performed using Microsoft Excel. All analyses will be completed per protocol since there is no intention to treat.

There will be no imputation of missing or implausible data, and any missing, implausible, or problematic readings will be excluded from the analysis. If the Lifelight software is unable to detect the participant’s face during the measurement period, this will be recorded in the electronic case report form, and the measurements will be deleted from the data set.

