## Results

The prototype Lifelight technology has been in development since 2016. The recruitment of participants for VISION-MD started in May 2021 but was compromised by the restrictions implemented to manage the COVID-19 pandemic, including restricting hospital access to the general public. Protocol amendments were thus made to enhance community recruitment, including the use of incentives such as chocolates or gift cards. In addition, the higher-resolution video recording (compared with the earlier VISION studies) supported reduction of the recruitment target to 1950, which is expected to yield sufficient high-quality measurements for machine learning and subsequent testing (reflected in a further protocol amendment). An additional amendment allowed the measurement of BP and pulse rate using devices other than the standard-of-care Welch Allyn devices (and indicated in the electronic case report form), as not all participating centers had the originally specified equipment.

Data for analysis will become available from September 2022, and the algorithms will be continuously refined to improve clinical accuracy. We anticipate that the final analyses to determine the performance of Lifelight against the targets set out in Table 2 will be complete in early 2023.

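### The only stated rule for sizing the reference cuff uses arm length and a lower limit, so cuff fit to arm circumference is not controlled and girth-related error in reference SBP cannot be separated from Lifelight error

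*Protocol article*

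**What the plan says.** Under VS measurement, "BP is measured using a standard clinical automatic sphygmomanometer", fitted with an "appropriately sized cuff (width at least two-thirds of upper arm length" on the nondominant upper arm, "or via an arterial line if fitted". The article gives no other sizing criterion, and arm circumference is not mentioned anywhere in it.

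Table 1 assigns BP measurement to subprotocols 1 and 4, with three measurements in each. Table 3 gives subprotocol 1 an indicative 1500 participants.

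The SBP target in Table 2 is that it "can be measured with standard deviation ≤8 mm Hg". Under Data Analysis, "The training data will be used to further develop the signal extraction and processing methodology" and "The test data will subsequently be used to determine the performance of Lifelight against the targets set out in Table 2". The standard-of-care reading is therefore the value that Lifelight is trained towards and also the value it is tested against.

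The Results section adds that "An additional amendment allowed the measurement of BP and pulse rate using devices other than the standard-of-care Welch Allyn devices". The device used is indicated in the electronic case report form.

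**The concern.** By specifying cuff size, the article accepts that size can affect the reading. The dimension it fixes is width relative to arm length. Two participants with equal arm length and very different girth face the same minimum width, and nothing in the bracket caps the width for a slim arm. How well the cuff fits around the arm is therefore left open.

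If cuff SBP carries an error that varies with girth, that error reaches the study by two routes. Where girth cannot be predicted from what the algorithm sees, the error appears in testing as extra Lifelight error. Where girth can be predicted, the algorithm can learn the error as if it were pressure, and a test against the same kind of reference would not reveal it. Error tied to the arm and the cuff is also a person-level error, so repeating the recording with the same cuff does not average it out. At stake is whether the SBP comparison with the 8 mm Hg limit reflects Lifelight or partly reflects the cuff.

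**Working it through.** The article states no figure for cuff error, so there is none to reproduce. Two checks were made.

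**1. What the rule allows**

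Input from VS measurement: minimum width = 2/3 × upper arm length. Arm lengths and girths below are assumptions.

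- Arm length 28 cm: 2/3 × 28 = 18.7 cm minimum width.
- Arm length 36 cm: 2/3 × 36 = 24.0 cm.
- Arm length 40 cm: 2/3 × 40 = 26.7 cm.

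Fit relative to girth for the 36 cm arm, at the minimum width:

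- 22 cm girth: 24/22 = 1.09
- 34 cm girth: 24/34 = 0.71
- 50 cm girth: 24/50 = 0.48

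The ratio varies by a factor of 50/22 ≈ 2.3 with every case compliant. Because there is no upper limit, the bracket also admits higher ratios.

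**2. What girth-related error would do to the SBP target**

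Input from Table 2: SD ≤ 8 mm Hg, a variance allowance of 64 mm Hg². Assumptions: the girth-related reference error has SD b, is independent of Lifelight's own error and is not learned by the algorithm; a device with true SD 7.5 mm Hg serves as the example.

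- SD left for Lifelight = √(64 − b²)
- Observed SD = √(7.5² + b²) = √(56.25 + b²)

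| Assumed b (mm Hg) | SD left for Lifelight | Observed SD if true SD is 7.5 |
|---|---|---|
| 1 | 7.94 | 7.57 |
| 2 | 7.75 | 7.76 |
| 3 | 7.42 | 8.08 |
| 4 | 6.93 | 8.50 |
| 5 | 6.24 | 9.01 |

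The example device reaches the limit when b² = 64 − 56.25 = 7.75, that is b = √7.75 ≈ 2.8 mm Hg. A constant offset would not change the SD; only the part that varies between people counts here. Table 2 also names a British Hypertension Society grade, but the article does not put it in figures, so it was not used.

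**The case against.** The strongest reply is that the text asks for an appropriately sized cuff and the bracket only adds a floor. Staff can still choose by girth above that floor, and an over-wide cuff on a slim arm need not count as appropriate. The article is a condensed account: the full protocol, site procedures and case report form are not shown, and the premeasurement observations may not all be listed. This stands in part. That the article mentions no record of circumference or cuff size is not a finding in itself. The finding is the rule that the article does state, because it fixes the wrong dimension and only from one side.

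A reader might go further and infer that reference SBP is biased by girth. The documents do not support that: they report no cuff sizes, arm girths or cuff error. A reader might also infer that cuffs too small for large arms push participants into higher SBP bands in subprotocol 1. That sits badly with the rule itself, whose minimum of 18.7 to 26.7 cm for assumed arm lengths of 28 to 40 cm is a high floor and makes a narrow cuff less likely where the rule is followed. Subprotocol 1 also recruits SBP below 100 mm Hg, and the Table 3 bands are indicative recruitment targets.

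Finally, one can produce a larger effect by assuming that 20-30% of participants are mis-cuffed by 5-10 mm Hg. The added SD is then 5 × √(0.2 × 0.8) = 2.0 to 10 × √(0.3 × 0.7) = 4.6 mm Hg, or 4/64 = 6% to 21/64 = 33% of the variance allowance. The arithmetic is right, but every input is assumed, so it illustrates and does not estimate.

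**Conclusion.** The point holds as a weakness in a stated rule. The sizing criterion does not control cuff fit to girth, and any girth-related error in cuff SBP would enter both training and testing without a way, in the article, to tell it apart from Lifelight error. Arterial-line readings are outside the problem.

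Its size is unknown. With an assumed girth-related SD of 1-2 mm Hg the effect on the 8 mm Hg target is small. From about 2.8 mm Hg it would change pass to fail, but only for a device already close to the limit (true SD 7.5 mm Hg in the example). These results assume independent errors. The extent to which Lifelight could learn the error depends on whether girth is predictable from its inputs, which the documents do not tell us. The change is worth making because it is cheap and the same reference serves both purposes, not because a bias has been shown.

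**What to change.** For all further cuff recordings, and at least for those going into the test set where that is still possible, replace the bracketed rule with selection by measured mid-upper-arm circumference within the range marked on the cuff by its manufacturer. Record circumference and cuff size in the electronic case report form, so that SBP error can be examined by girth. The Introduction says that later data will be used for testing, so a change may still reach those recordings.

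For recordings already made, identify which used a cuff under the length rule and which an arterial line, and report this as a limitation. An analysis with and without the length-rule recordings would help little, since nearly all existing cuff readings are likely to fall under that rule, and girth cannot be recovered if it was not recorded. If the full protocol already sizes cuffs by circumference, the published wording should simply be corrected.

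The cost is a tape measure, a few seconds per session and two form fields. The downside is a mix of old-rule and new-rule data, which needs a flag.
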